Several assumptions were considered for the sample size calculation [26]. The first assumption was that mean LAZ (our primary outcome variable) for 18–23 months old children in the comparison arm will be −2.0, and standard deviation of mean LAZ in both intervention and comparison arms will be 1, based on the mean HAZ reported in this age group in the BDHS 2011. These BDHS 2011 [25] parameters were the latest available during this protocol development. The estimates were still valid in 2015 since the latest BDHS (2014) showed similar stunting rates in *Sylhet* division [11]. Second, a 0.4 difference in mean LAZ score was expected in intervention arms compared to comparison. As the third assumption, we considered an 80% power and 5% alpha; the inter-cluster correlation coefficient of 0.06, derived from the design effect for HAZ in BDHS 2011, was used for adjustment of clustering effects. Fourth, the ratio between 4 intervention and 1 comparison arms was set at 1:1:1:1:1. Taking all the above assumptions into account, the Stata SE 13 software calculated the sample size to be 175 children per arm, which can be yielded from 25 clusters. However, to examine the secondary outcome variables between the comparison arm and individual intervention arm with a higher statistical power, the sample size in the comparison arm was doubled, thus the ratio between participant numbers in each intervention arm and comparison arm was raised to 1:2, respectively. The final allocation ratio of study participants was thus 1:1:1:1:2 for intervention arm 1: intervention arm 2: intervention arm 3: intervention arm 4: comparison arm 5. Thus, the final sample size was 175 children in each intervention arm and 350 children in the comparison arm. Considering the characteristics of the intervention, however, enrolment was during pregnancy. We therefore considered the following losses- 11% pregnancy loss due to abortion and still births (personal communication from Health and Demographic Surveillance System run by icddr,b at Mirzapur, Tangail), a 4% mortality in the first two years of life [25], 15% losses due to non-consent to participate by eligible women and loss-to-follow up. Loss-to-follow up includes refusal and migration out of study area. Thus, final sample size considering participant recruitment during pregnancy was 250 pregnant women in each intervention arm and 500 pregnant women in the comparison arm which is expected to yield the required number of children at 24 months from the enrolled cohort.

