### Trial outcomes and measurements

#### Primary outcomes

The primary outcome measure will be the LAZ of children at 24 months of age based on WHO MGRS 2006 child growth reference. This will be calculated from the child’s age in months and length on associated ages. Length is measured at age 7–10 days, then monthly from 1 to 6 months, and at 9^th^, 12^th^, 15^th^, 18^th^, 21^st^ and 24^th^ months of age, with locally manufactured collapsible length boards (precision 1 mm).

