### Statistical analysis plan

Data analysis to detect change of the primary outcome (mean LAZ) will be conducted with length measured at 1, 3, 6, 9, 12, 15, 18, 21 and 24 months of age using t-tests assuming LAZ will satisfy the normality assumption. Longitudinal assessment of significance using lag time of stunting (mean length > −2SD below median of WHO reference population) will be done by the log rank test, followed by fitting a Cox proportional hazards model for each intervention arm to determine the change in risk of stunting compared to the comparison arm. Multiple linear regression will be employed to quantify the effect of intervention in each intervention arm compared to the comparison arm in terms of mean LAZ change and some secondary continuous outcome measures including changes in mother’s weight, birth weight, diarrhoea morbidity. Logistic regression will be used on binary outcome variables which comprise most of our secondary outcomes measures (e.g. – EBF and breastfeeding initiation within 1 h of birth). All these models will be controlled for possible confounders (household food security, educational background and SES) if randomisation of the clusters does not control for differences in these factors at baseline. For regression models, we shall consider random effects of clustering. All analysis will be intention-to-treat. Quantitative data analysis will be done using Stata SE 14.2 (StataCorp LP, College Station, Texas, USA).

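### The 24-month LAZ comparison is fixed as a cross-sectional t-test, so the earlier lengths of children lost before 24 months do not inform the primary contrast

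*Protocol article*

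**What the plan says.** The Statistical analysis plan section of the protocol article makes four relevant statements.

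- Mean LAZ is tested with "length measured at 1, 3, 6, 9, 12, 15, 18, 21 and 24 months of age using t-tests".
- "Multiple linear regression will be employed to quantify the effect of intervention in each intervention arm compared to the comparison arm". This regression is described by the change in LAZ and by several secondary measures; no age is attached to it.
- "For regression models, we shall consider random effects of clustering". Cluster is the only random effect named; there is none for the child.
- A longitudinal analysis of stunting "will be done by the log rank test, followed by fitting a Cox proportional hazards model for each intervention arm".

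The section adds that "All analysis will be intention-to-treat", without defining the term further.

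Under Primary outcomes, the endpoint is LAZ at 24 months. "Length is measured at age 7–10 days, then monthly from 1 to 6 months", and then every third month from 9 to 24 months.

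Under Sample size, the trial is sized on children present at 24 months: 175 per intervention arm and 350 in the comparison arm. The losses allowed for are 11% pregnancy loss, 4% child mortality and 15% for non-consent and loss to follow-up combined. "Loss-to-follow up includes refusal and migration out of study area".

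**The concern.** A t-test at 24 months has nothing to say about a child who was measured repeatedly to, say, 18 months and then moved away. That child's growth is known almost to the endpoint, yet it carries no weight in the primary comparison. The same holds for a regression of 24-month LAZ whose only random effect is for cluster.

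The comparison is then among completers. If the arms lose different proportions of children, and shorter children are more (or less) likely to be lost, the completers' difference is not the difference among all surviving children. Arm-differential loss is conceivable: intervention families have repeated counselling visits and, in three arms, monthly supplement sachets, while comparison families receive routine services only. What is at stake is the estimate on which the trial's main conclusion rests.

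**Working it through.** **1. The plan's own loss figures.** Adding the losses gives 11% + 4% + 15% = 30%. Then 175/0.70 = 250, 350/0.70 = 500 and 1500 × 0.70 = 1050, which are the published figures. The 24-month comparison is therefore planned on about 70% of enrolled pregnancies.

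**2. How many lost children could have earlier lengths.**
- Pregnancy loss (11%): no length is possible.
- Death (4%): there may be earlier lengths, but there is no 24-month LAZ to recover.
- Remaining 15%: 0.15 × 1500 = 225. This is an upper limit, because the 15% includes non-consent and the split is not given; women lost during pregnancy also leave no length.
- Surviving children: 1500 × (1 − 0.11 − 0.04) = 1275, and 225/1275 = 17.6%.

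**3. Lengths available.** One at 7–10 days, six at months 1–6 and six at months 9–24 make 13, of which 12 precede month 24. The t-tests list nine of the 13 ages, each taken alone.

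**4. Possible bias.** Assume that loss is logistic in the last recorded LAZ, with slope b per SD (shorter children lost more often), and that this LAZ correlates ρ with 24-month LAZ (SD 1, from the plan). To first order, completers' mean LAZ is shifted upwards by ρ × b × (loss proportion). The bias in intervention minus comparison is then about −ρ × b × (p_comparison − p_intervention). For example, ρ = 0.8, b = 0.5 and loss of 8% v 18% give −0.8 × 0.5 × 0.10 = −0.040. The approximation overstates the bias for steep slopes. Numerical integration over ρ = 0.8–0.9 gives:

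| Assumed loss, intervention v comparison | Slope b | Bias (LAZ) |
|---|---|---|
| 15% v 15% | any | 0 |
| 12% v 16% | 0.5 | −0.015 to −0.017 |
| 8% v 18% | 0.5–1.0 | −0.04 to −0.08 |
| 5% v 20% | 0.5–1.0 | −0.06 to −0.11 |

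Reversing the imbalance reverses the sign.

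A second route gives a similar size. Suppose that 5%, 10% or 15% of those enrolled are lost survivors, that loss is selective in one arm only, and that the lost differ from those measured by 0.25–0.5 LAZ. The lost fractions of survivors are 0.05/0.75 = 0.067, 0.10/0.80 = 0.125 and 0.15/0.85 = 0.176. The shifts run from 0.067 × 0.25 = 0.017 to 0.176 × 0.5 = 0.088.

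**5. Precision.** With ICC 0.06, power = Φ(0.4/√V − 1.96), where V = [1 + 6 × 0.06]/175 + [1 + 13 × 0.06]/350 = 0.01286. The SE is 0.113 and power is 94.2%. If all 15% were lost survivors and ρ = 0.9, the effective number per intervention arm would be 250 × (0.70 + 0.81 × 0.15) = 205 (twice that in comparison), the SE 0.108 and power 95.9%. With 5% and ρ = 0.7 the number is 181 and power is 94.6%. The gain in SE is at most about 5%.

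**The case against.** A reader might infer that the plan contradicts its own intention-to-treat statement. The documents do not support that. The term is not defined further, and analysed as allocated is an ordinary meaning with which a t-test is compatible. No complete-case rule is written either, and the handling of missing values may sit in a document not shown, so its absence is not the point here.

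A reader might also infer that children lost early are discarded and that every regression is run age by age. The ages are attached only to the t-tests; the regression is described by mean LAZ change. A child last seen at 15 months still enters the t-tests at the earlier listed ages and can give censored time to the log-rank and Cox analysis. Neither of these, however, estimates the 24-month contrast.

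The mechanism for differential loss is also uncertain. Lengths are taken by data collectors who are separate from the counselling workers, the measurement schedule is not described as differing by arm, and no figure for loss by arm is given. The bias figures rest on chosen loss gaps and slopes. The mixed model's near-zero bias holds because loss was assumed to depend on recorded LAZ. If loss instead depends on unrecorded 24-month LAZ, and earlier LAZ correlates only 0.4 with it, most of the bias stays: about −0.048 becomes −0.040 at 8% v 18% with slope 0.5.

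All of this stands and limits the point. What it does not remove is that the named primary test cannot use lengths that the trial collects for this outcome.

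**Conclusion.** The point holds as a cheap improvement to a named method, not as a proven contradiction or a demonstrated bias. The 24-month comparison is fixed as a cross-sectional test among children measured at that age. Earlier lengths of at most about 225 lost survivors out of 1500 pregnancies, probably fewer, do not inform it. The resulting bias ranges from zero with equal loss to about 0.1 LAZ, roughly a quarter of the 0.4 target, under strong assumed imbalance; with a 4-point gap in loss and slope 0.5 it is under 0.02. The loss rates by arm, the slopes and the correlations are all assumptions. Lost precision alone would not justify a change.

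**What to change.** Make the primary estimate the contrast of each intervention arm with the comparison arm at 24 months, taken from one linear mixed model for LAZ on all scheduled lengths. Fixed effects: categorical age, arm, arm-by-age, and union or block. Add a random effect for cluster and a within-child covariance, unstructured or, if that does not converge, a simpler structure named in advance. With 13 ages an unstructured matrix has 13 × 14/2 = 91 parameters, so the fallback is needed.

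Alongside this:
- keep the 24-month completer analysis, with clustering accounted for, as a sensitivity analysis;
- tabulate pregnancy loss, child death and loss to follow-up by arm;
- state how children who die are treated, since the model would otherwise implicitly project a 24-month LAZ for them; for example, restrict the target to survivors in a sensitivity analysis;
- say that intention-to-treat means analysed as allocated, and name the set of children analysed.

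The cost is modest extra analysis work in the software already planned, with no change to data collection. The model relies on loss being explained by recorded LAZ, which is a weaker assumption than that of the unadjusted completer t-test but is still an assumption.

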## Discussion

Our primary study aims to investigate the effects of 5 nutrition-specific *preventive* interventions, adapted from the Lancet’s modelled intervention list (Bhutta et al. [2013]), delivered in different bundles to improve the LAZ score from conception to two years of age in a food-insecure area of rural Bangladesh.

One of the major strength of this study is its depth (multiple community-friendly evidence-based intervention packages) and breadth (first 1000 days with interventions directed at both mother and child). The results will attempt to clarify the effects of counselling combined with prenatal nutritional and/or complementary food supplementation on linear growth of the child. In addition, our study will also explore the interventions impact on nutritional intake during pregnancy, gestational weight gain, birth weight and IYCF practices. The cluster RCT design in a community setting will offer robust evidence on the effectiveness of the bundles compared to the comparison arm where routine practices will run unabated. The relatively homogenous study population in a food-insecure area would further strengthen our inferences, as we would expect minimal inter-cluster differences that would otherwise potentially confound associations.

We are also one of the few studies in Bangladesh using a bespoke digital platform for intervention delivery and monitoring of coverage. Android-based handheld devices are being used by CHW to automate planning of visit schedules as well as aid counselling sessions by providing the appropriate BCC content based on the gestational age and subsequently, age of the child. Visual aids and video demonstrations of good practices included in the electronic counselling modules are expected to result in improved interaction and retention of key messages by the participants. Field level android-based devices are web-linked to a central server to leverage the opportunity for real time monitoring of community health workers performance and coverage of intervention delivery. Thus, this study will contribute to the growing body of implementation research on benefits and challenges of integrating electronic platforms in delivering counselling and supplemental interventions in a community setting.

Recently, the government of Bangladesh undertook significant efforts to digitize service delivery in all spheres of health systems including frontline and community level health care providers who are responsible for delivering nutrition interventions [39]. This trial will provide a timely and pertinent contribution to the knowledge base of use of electronic platforms in not only recording and reporting of service utilization but also aiding the community workers in nutrition service delivery at scale.

A limitation of our study includes not being able collect biological samples from study participants due to funding constraints; this would have allowed us to investigate potential biological mediators of the effect of nutrients as well as exploring inherited differences in metabolism predisposing to the risk of stunting. Our study also does not look at knock-on effects beyond 2 years of age.

We anticipate that the results from this cRCT will have policy-level implications in prioritizing a set of interventions when addressing stunting - whether it is behaviour change communication only or combined with prenatal and/or post-natal nutritional supplementation.

## Trial status

Recruitment has been completed. Intervention and data collection is ongoing.

## Abbreviations

ANC: Antenatal check-up
BCC: Behaviour change communication
BDHS: Bangladesh Demographic and Health Survey
BMI: Body mass index
CF: Complementary feeding
CFS: Complementary food supplementation
CHW: Community health workers
cRCT: Community-based cluster randomised controlled trial
EBF: Exclusive breastfeeding
FRA: Field research assistant
FW: Field supervisors
HFS: Household food security
IYCF: Infant and young child feeding practices
KAP: Knowledge attitude and practice
LAZ: Length-for-age Z score
LMP: Last menstrual period
LNS: lipid-based nutritional supplement
MIS: Management Information System
MUAC: Mid-upper arm circumference
NGO: Non-government organisations
PNS: Prenatal nutritional supplementation
RDA: Recommended dietary allowance
SD: Standard deviation
SDG: Sustainable development goals
SES: Socio-economic status
WASH: Water, sanitation and hygiene
WHO MGRS Child Growth Reference: WHO Multicentre Growth Reference Study Child Growth Reference
